#### 2.6.4. Analyses for Secondary Endpoints

Secondary analyses will determine the effect of sleep quality on subsequent food intake and physical and cognitive performance. Thus, all the secondary quantitative endpoints (TST; SOL; WASO; variation in sleep stages; DLMO measured by salivary assays; blood markers of sleep, inflammation, and food intake; resting energy expenditure; 24 h food intake for the next day; measurement of energy and macronutrient intake assessed by the weighing method during meals consumed ad libitum; metabolic fitness; muscle fatigability; and cognitive performance assessed by the cognitive test battery) will be studied as described for the primary endpoint. These analyses will be carried out for each of the study groups (adolescent rugby players vs. adolescents with obesity). In a second step, the two groups of subjects will be pooled; the aforementioned statistical approaches will be used with an additional fixed group effect and the associated interactions.

A sensitivity analysis will be performed to study the statistical nature of missing data and to determine the most appropriate approach for imputing missing data.

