## Abstract

Disturbed sleep is common in adolescents. Ingested nutrients help regulate the internal clock and influence sleep quality. The purpose of this clinical trial is to assess the effect of protein tryptophan (Trp)/large neutral amino acids (LNAAs) ratio on sleep and circadian rhythm. Ingested Trp is involved in the regulation of the sleep/wake cycle and improvement of sleep quality. Since Trp transport through the blood–brain barrier is competing with LNAAs, protein with higher Trp/LNAAs were expected to increase sleep efficiency. This randomized double-blind controlled trial will enroll two samples of male adolescents predisposed to sleep disturbances: elite rugby players (n = 24) and youths with obesity (n = 24). They will take part randomly in three sessions each held over a week. They will undergo a washout period, when dietary intake will be calibrated (three days), followed by an intervention period (three days), when their diet will be supplemented with three proteins with different Trp/LNAAs ratios. Physical, cognitive, dietary intake, appetite, and sleepiness evaluations will be made on the last day of each session. The primary outcome is sleep efficiency measured through in-home electroencephalogram recordings. Secondary outcomes include sleep staging, circadian phase, and sleep-, food intake-, metabolism-, and inflammation-related biochemical markers. A fuller understanding of the effect of protein Trp/LNAAs ratio on sleep could help in developing nutritional strategies addressing sleep disturbances.

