#### 2.3.1. Objectives

The primary objective of this study is to investigate the effect of proteins with different Trp/LNAAs ratios on sleep efficiency (Figure 1). Secondary objectives are to determine the effect of protein Trp/LNAAs ratio on:Other sleep outcomes such as sleep staging, sleep onset latency (SOL) and wake after sleep onset (WASO)Circadian phase measured by DLMOMorning cortisol peakBiochemical markers related to sleep, food intake, metabolism, and inflammationMetabolic fitness measured by indirect calorimetry on submaximal testMuscle fatigue measured by time of maintenance of muscle strengthCognitive performances measured by a battery of tests including Stroop, trail marking, barrage, California verbal learning, and multiple object trackingEnergy intake and proportion of that energy derived from each macronutrient class (carbohydrate, fat, and protein) measured on meals offered ad libitumAppetite sensations (visual analog scales)Sleepiness rate (Karolinska scale)

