#### 2.3.2. Experimental Sessions

At baseline, participants will undergo numerous assessments for anthropometry, body composition, and resting metabolic rate (RMR). They will complete the Morningness–Eveningness Questionnaire for Children and Adolescents (MEQ-CA) to determine their chronotype [41], the self-report Pittsburgh sleep quality index (PSQI) to measure subjective sleep quality [42], the Epworth sleepiness scale (ESS) to measure daytime sleepiness [43], and the international physical activity questionnaire (IPAQ-SF) to estimate habitual physical activity level [44].

After the baseline and one week before to the experimental session launch of each group, time in bed (TIB) will be fixed, and sleep–wake cycle will be continuously monitored using accelerometry. Participants will also be equipped with the Sleep Profiler-PSG2 TM (Advanced Brain Monitoring, Carlsbad, CA) to familiarize them with sleeping with the device. Thereafter, three sessions will be conducted. Each session will be held over a week (Figure 2). Given the potential effect of electronic media (smartphone, laptop, etc.) on sleep and circadian rhythm [45], their evening use will be prohibited during the study.

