To limit inter-individual differences, participants will undergo a washout period (three days). During this period, their diet will be set to the recommended dietary allowance (RDA) (1.8 × basal metabolism for athletes and 1.3 × basal metabolism for adolescents with obesity) with protein intake fixed at 1.2 g.kg^−1^. The RDA will be calculated individually for each subject. Three meals and a snack will be offered each day. The meal trays will be prepared in advance and will be the same between sessions. At the last night of washout (Night 3), five saliva samples will be collected to capture DLMO (3, 2, and 1 h before bedtime, bedtime, and 1 h after bedtime). Participants will be fitted with the Sleep Profiler-PSG2 TM for the night. On awakening next day, two saliva samples (on awakening and 60 min later) will be taken to measure morning cortisol level, and blood samples will be collected in the fasting state to measure several biochemical markers related to sleep, food intake, metabolism, and inflammation. During the next three days, dietary intake will be supplemented with protein shakes (PROT-REF = 0.04, PROT1 = 0.07, or PROT2 = 0.11). From Day 4 to Day 6, the diet will be iso-energetic to the washout period (Days 1—3) diets. However, protein intake will be raised from 1.2 to 1.6 g.kg^−1^ through (PROT-REF, PROT1, or PROT2) shakes and intake from other macronutrients will be adjusted accordingly. Similar to Night 3, participants will collect five saliva samples and undergo electroencephalogram (EEG) recordings during Night 6.

At Day 7 (Figure 3), on awakening, saliva samples and blood samples will be collected. Food will then be offered ad libitum in four meals (breakfast, lunch, afternoon snack, and dinner) representing 24 h energy intake. Participants will be asked to fill out visual analog scales for their appetite sensations and sleepiness level throughout the day. After breakfast, participants will take part in evaluations including metabolic fitness on submaximal test, muscle fatigue measured by time of maintenance of strength of the knee extensor muscles, and cognitive performance measured by a battery of tests (Stroop, trail marking, trail-making task, barrage test, California verbal learning, and multiple object tracking).

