#### 2.6.3. Analyses for Preliminary Endpoint

Intention-to-treat analysis will be considered for the primary analysis. To prevent attrition bias, imputation of missing data is planned. The statistical analysis plan also provides for an additional per-protocol analysis.

To study the effect of quality of protein intake on quality of sleep, the primary analysis will be performed using statistical tests for repeated correlated data. Mixed models to take into account between and within subject variability will be used, considering the following fixed effects: study of protein (PROT-REF, PROT1, and PROT2), point-time evaluation, period, order, and carry-over together with their interactions (including *protein × point-time evaluation*), with subject as a random-effect. Then, the group effect (adolescent rugby players vs. adolescents with obesity) will also be studied, and special attention will be paid to the interaction status *group × proteins*.

These analyses will be followed if necessary (p < 0.05) by a post-hoc test suitable for multiple comparisons such as the Tukey–Kramer test. Multivariable analysis should be used to complete the aforementioned analyses, to take into account possible confounding factors including age and BMI. Results will be expressed in terms of effect sizes and 95% confidence intervals.

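### The stated secondary question, the effect of sleep quality on intake and performance, cannot be answered by the model assigned to it, which has no sleep term; resting energy expenditure is listed as an endpoint but described only at baseline

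*Protocol article*

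**What the plan says.** The Protocol article describes the secondary question in two ways.

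- Section 2.3.1 (Objectives): "Secondary objectives are to determine the effect of protein Trp/LNAAs ratio on" a list of outcomes that includes metabolic fitness, muscle fatigue, cognition and energy intake. The exposure is the protein.
- Section 2.6.4 (Analyses for Secondary Endpoints): "Secondary analyses will determine the effect of sleep quality on subsequent food intake and physical and cognitive performance". The exposure is sleep.

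Section 2.6.4 then lists 12 quantitative endpoints and says that they "will be studied as described for the primary endpoint". The model meant is in section 2.6.3, a mixed model with a random subject effect, "considering the following fixed effects: study of protein (PROT-REF, PROT1, and PROT2), point-time evaluation, period, order, and carry-over together with their interactions". A complementary multivariable analysis covers "possible confounding factors including age and BMI". Neither description names a sleep variable as a predictor.

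On timing, the Abstract says: "Physical, cognitive, dietary intake, appetite, and sleepiness evaluations will be made on the last day of each session". On resting metabolism, section 2.3.2 says: "At baseline, participants will undergo numerous assessments for anthropometry, body composition, and resting metabolic rate (RMR)". Section 2.4.1 also places that measurement among the baseline assessments, yet resting energy expenditure is one of the 12 endpoints in section 2.6.4.

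**The concern.** A model yields effects only for the terms it contains. If the question is what sleep does to next-day intake or performance, sleep has to be a predictor. In the model cited, sleep appears only as an outcome, when the sleep endpoints themselves are analysed.

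The difference matters because protein is randomised and sleep is not. The document itself allows protein to act by routes other than sleep: the Introduction mentions amino acids stimulating excitatory hormones, and section 2.4.2 plans assays of appetite-related hormones. A Day 7 protein difference in intake or cognition could therefore arise with no change in sleep. Under the opening sentence of section 2.6.4, a reader could still take it for a sleep effect.

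Two smaller mismatches follow from applying the primary model to everything. That model is built around a pre/post change within each session, and some endpoints have no pre value. One listed endpoint has no described measurement after any shake.

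**Working it through.** The plan gives no figure of its own on this point. The check sets endpoints against measurement times and then asks what the section 2.6.3 model can estimate.

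**1. Exposure against model.** Fixed effects in section 2.6.3: protein, time point, period, order, carry-over and their interactions. Named confounders: age and BMI. Sleep terms: none. The coefficients describe protein, not sleep.

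**2. Measurement times of the 12 endpoints in section 2.6.4.**

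| Endpoints | Measured | Count |
|---|---|---|
| Total sleep time, onset latency, wake after onset, sleep stages, DLMO | Nights 3 and 6 of each session (2.3.2) | 5 |
| Blood markers | Days 4 and 7 of each session (2.4.2) | 1 |
| 24 h intake, energy and macronutrient intake, metabolic fitness, muscle fatigability, cognition | Day 7 of each session (Abstract, 2.3.2, 2.4.3) | 5 |
| Resting energy expenditure | Baseline only in the visible text (2.3.2, 2.4.1) | 1 |

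So 6 of 12 have a pre/post pair, 5 of 12 (42%) are Day 7 only, and 1 of 12 is baseline only. Every outcome named in the opening sentence of section 2.6.4 falls in the Day-7-only row.

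**3. Estimability.** Assume 24 participants in one population, 3 periods, all 6 treatment sequences used equally, and complete data. The article does not list the sequences, so 6 is an assumption. Of the interactions, only protein by time point is included.

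Columns: intercept 1 + protein 2 + period 2 + order 5 + carry-over 2 = 12. Adding time point 1 and protein by time point 2 gives 15.

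- Pre/post data (24 × 3 × 2 = 144 rows): rank 15 of 15. All terms are estimable.
- Day-7-only data (24 × 3 = 72 rows): rank 12 of 15. The three time-point columns cannot be separated from the rest.
- Day-7-only data without those three columns: rank 12 of 12. The protein main effect is estimable.

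In the last case, 72 values less 24 participant means leave 48 within-subject degrees of freedom. Taking off protein 2, period 2 and carry-over 2 leaves 42 for error, which is ample for a protein comparison.

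**4. Resting energy expenditure.** One value per participant gives 24 values. Less 24 participant means, this leaves 0 within-subject degrees of freedom. The value also precedes all three proteins, so no protein effect can be estimated from the schedule described.

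**5. Could the sleep question be answered with the data collected?** Yes. Sleep is recorded on Night 6 of each session, the night before the Day 7 tests. Write S_ij for Night 6 sleep efficiency of participant i in session j, and S̄_i for his mean over sessions:

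Y_ij = protein + period + sequence + β_W (S_ij − S̄_i) + β_B S̄_i + u_i + e_ij

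Within-subject error degrees of freedom: 48 − 2 (protein) − 2 (period) − 1 (β_W) = 43. The model can be fitted, and β_W is the within-subject association. It remains observational, because sleep follows randomisation and may itself depend on the protein.

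**The case against.** The case for leaving the text alone is as follows. Section 2.3.1 states the secondary exposure plainly as the protein ratio. The list in section 2.6.4 includes sleep variables, which cannot sensibly be outcomes of sleep quality, so its opening sentence may be loose wording that does not govern the list. The model described contains protein and tests what the objectives ask. Which terms apply to which endpoint is detail that a condensed article may leave to the full analysis plan.

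Much of this stands, and it limits the point. Four stronger readings are tempting, and the documents do not support them:

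- *Most secondary endpoints lack a pre-intervention value.* Only 5 of the 12 listed are Day 7 only and 1 is baseline only; 6 have a pre/post pair. By the ten objectives in section 2.3.1, six are Day 7 only, but the analysis list is the one tied to the model.
- *The Day-7-only endpoints cannot be analysed.* They lose the interaction with time point and keep the randomised protein contrast.
- *A protein difference will be reported as an effect of sleep.* No passage says so. The Discussion asks only whether sleep changes are accompanied by better performance. Misreading is a risk, not a stated plan.
- *Resting energy expenditure has no post-intervention data and must be deleted.* Figures 2 and 3, the protocol overview and the Day 7 timeline, are not shown and might include a repeat.

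The objection does not remove the conflict itself. Section 2.6.4 states in the text, as the purpose of the secondary analyses, a question that its own model does not address and that differs from section 2.3.1. This is something the article states, not a detail it omits.

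**Conclusion.** The point holds in a limited form and should be corrected. The stated secondary question has no matching term in the assigned model, and two sections name different exposures for the same outcomes. This affects all five intake, physical and cognitive endpoints among the 12 listed. For those five the protein by time-point term does not apply, which matters little because the protein main effect survives. Resting energy expenditure cannot show a protein effect under the schedule described in the text.

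The conclusion rests on the visible text being complete about when resting metabolism is measured, and the rank check rests on the assumed six sequences and complete data. The primary endpoint, the sample size and the randomised protein comparisons for the other secondary endpoints are not affected.

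**What to change.** 1. In section 2.6.4, state the secondary estimand as the effect of the protein, in line with section 2.3.1.
2. For the five Day-7-only endpoints, specify the protein main effect with period and sequence, a random subject effect and no time-point term. Treat carry-over as for the primary endpoint.
3. Reconcile resting energy expenditure with the schedule: remove it as an endpoint, or state when it is measured within sessions.
4. If the sleep question is to be kept, answer it in a separate model labelled exploratory. Include that session's Night 6 sleep efficiency, for example split into within-subject deviation and subject mean as in the formula above, and report the result as an association.

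The cost is a few sentences of analysis-plan wording and a small amount of extra analysis. No new data, visits or participants are needed.

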## 3. Discussion

We describe the rationale and design of a randomized controlled trial to evaluate the effect of protein Trp/LNAAs on sleep in adolescents (either elite rugby players or with obesity). Emerging literature warns about the precariousness of adolescents’ sleep, especially for those practicing elite sport or with obesity. Cumulated demands of being both high school students and junior athletes may contribute to poor sleep, especially as elite sport pressures such as high training volume, late evening exercise, travel, and competition are linked to sleep disturbances [7]. For the second population, studies underlined that adolescents with obesity were particularly prone to several psychopathologic conditions, including anxiety and chronic stress, which affect the hypothalamic–pituitary–adrenal axis and increase the arousal/sympathetic nervous systems activities [58]. Furthermore, the literature points to a complex interaction between sleep, obesity and metabolic disruption [12,13]. Excess adiposity may lead to dysregulation of the adipose secretory factors that contribute to the development of low-grade systemic inflammation marked by an over-release of several pro-inflammatory markers. The results of the HELENA study in adolescents show an association between disturbed sleep and systemic inflammation [59].

The PROTMORPHEUS protocol also seeks to clarify whether sleep variation through protein with higher Trp/LNAAs will be accompanied by improved in physical and cognitive performance, along with dietary intake, appetite, and sleepiness sensations.

The effect of Trp on sleep was first derived from the serotonergic hypothesis (Figure 4). Serotonin (5-HT) is synthesized from Trp circulating in the brain by a two-step procedure in raphe neurons. 5-HT, in turn, is a precursor of melatonin, and both help regulate of sleep-wake behavior [60]. However, Trp is an essential amino acid whose sole source is the degradation of dietary proteins. The passage of Trp to the brain is ensured through carriers at the BBB. However, carrier transport depends on other competitive amino acids (LNAAs leucine, isoleucine, valine, phenylalanine, and tyrosine). Increased brain uptake of Trp does not therefore depend only on Trp but rather on the blood Trp/LNAAs ratio [37]. Given that melatonin and 5-HT are synthesized from Trp, we can reasonably expect an increase in their levels in the brain depending on the Trp/LNAAs ratio of the administered protein. This hypothesis has been validated in animal models [61]. Moreover, Minet-Ringuet et al. (2004) also showed that protein intake restored altered sleep effectively, especially slow-wave sleep (SWS) depending on protein Trp/LNAAs ratio [62]. However, to our knowledge, no studies have been done to test this hypothesis in humans. The study by Markus et al., (2005) found that evening intake of protein rich in Trp increased the ratio of plasma tryptophan to the sum of LNAAs with an improvement in next-day alertness and cognitive performance [63]. However, objective sleep quality and staging were not measured in that study.

PROTMORPHEUS has several strong points. To our knowledge, it is the first protocol investigating the effects of such an intervention in humans under ecological free-living conditions. Each adolescent participating in the study will be followed for three weeks during which their food intake, sleep, and physical activity will be controlled and recorded continuously. To improve the feasibility of the study, the methodology is designed to be minimally intrusive. Instead of conducting the study in the laboratory, which could make it extremely intrusive, we will let participants spend their nights in their habitual sleeping environment. More importantly, previous studies found that spending the night in laboratory conditions could introduce bias in sleep assessment. Ambulatory measures will therefore be used in the usual sleep environment, including minimally invasive electroencephalogram recordings and a simplified circadian phase assessment method. Recruited adolescents will be living at boarding schools and the investigators will move on-site to ensure that the measurements are conducted in appropriate conditions. Given the density of measures and the time constraint during evaluation (Day 7), workshops will be set up. Participants will switch between the workshops in an assisted way with the same order between the sessions.

Latent factors related to both obesity and/or sleep may affect outcomes of studies investigating the effect of dietary intervention on sleep. For instance, we already showed in previous works that physical activity could affect sleep in adolescents with obesity [64]. Therefore, we underline that these factors should be systematically quantified and added as confounders. Laboratory PSG is considered as the gold standard for sleep assessment. The absence of this measure is perhaps the main limitation of this study. However, gold standard PSG is not a viable option in the context of this research because: (i) it is cumbersome (two measures per session); (ii) differences in sleep quality may result from changes in sleeping environment; and (iii) the protocol already makes strong demands on the adolescent’s personal life during the protocol (three consecutive weeks). The ambulatory wearable device to be used includes all the major aspects of PSG: three EEG channels, airflow, thorax, and abdomen belt and pulse oximetry. Its measurements have been validated and yield results comparable to polysomnography in assessing sleep staging and several other parameters. However, this study is also limited by a small sample size and does not include female subjects. Although it is interesting to look for gender effect, the control of menstrual cycle phase in adolescent girls would be complicated and incompatible with such a study design. Previous studies have shown that menstrual cycle phase impacts sleep, circadian rhythm, and food intake, which could lead to biased assessments [65]. Finally, the effect of such an intervention in the medium and long term remains to be determined and would be interesting. Motivating the adolescents to follow this study protocol for a longer period is challenging and may severely penalize the feasibility of the study. However, previous studies already showed that dietary manipulation affect sleep significantly even over a shorter period of time than that of this study [66,67].

